### Trial design {8}

The trial design is a borough-stratified, four-arm, factorial-design, cluster RCT that targets 64 randomly selected buildings (16 buildings per arm) in separate NYCHA developments. We are recruiting and following 8 randomly selected residents stratified by smoking status − 4 smokers and 4 non-smokers - per building (n = 512) into four arms: (1) reduction/cessation, (2) resident endorsement, (3) reduction/cessation plus resident endorsement and (4) the standard approach (128 participants per arm) as shown in Fig. 1. A partnering community-based organization, Health People, Inc., specializing in peer-to-peer health education will train and supervise peer educators (PEs) who will then deliver the designated interventions. Quantitative assessments via survey questionnaire, salivary cotinine measurements, as well as sensory building observations will be used to measure outcomes. We will be evaluating the efficacy of compliance support interventions in reducing personal smoking and exposure to second-hand smoke in public housing. In addition, we will also determine if the tobacco retail environment surrounding a given public housing building moderates the relationship between compliance support interventions and smoking-related outcomes.

This study applies the *Social Ecological Theory*. This framework posits that multiple intersecting levels of influence affect human behavior and actions (48), and can provide a more comprehensive understanding of smoking, cessation, and tobacco-related health disparities (49).This includes individual, relationship, community, and societal level of influences. Applying this theory to our study, public housing residents are influenced by interpersonal interactions among residents (micro-level), secondhand smoke exposures within residential settings (meso-level), and tobacco retail environment and tobacco control policies (macro-level). Previous work has targeted each of these aspects for smoking cessation interventions (47, 50–52), examined the impact of smoke-free air laws on quitting intentions (53); and found the perception of social capital and social participation are associated with increased smoking cessation (54–56).This resonates with the strategies that are being introduced in the resident endorsement intervention where social capital and social participation are foundational to the success of the intervention to gain public support for the smoke-free policy. However, our interventions are uniquely designed to extend beyond what has been found in prior work by capturing multiple facets of this theory by targeting various levels simultaneously (see Fig. 2) (51, 57, 58), reducing barriers to the use of counseling and medication in quit attempts (59), and leveraging social capital and social participation in housing communities to reduce individual smoking behaviors and exposures to secondhand smoke (60–63).

## Methods: Participants, Interventions And OutcomesStudy

### Setting {9}

The New York City Housing Authority (NYCHA) is the largest public housing provider in the US with over 500,000 residents across 335 developments throughout the city via conventional public housing, Section 8, and Permanent Affordability Commitment Together (PACT) or Rental Assistance Demonstration (RAD) housing (64). Though NYCHA is unique in its size and organization of buildings, it is characteristic of other public housing settings in that its entire portfolio of buildings and campuses are subject to smoking bans. Additionally, the resident profiles are similar across socioeconomic status and smoking behaviors. For feasibility, this study will be conducted at public housing sites located across two New York City boroughs where public housing is most concentrated: Manhattan and the Bronx. There are a total of 159 developments and 93,012 current dwelling apartments in these two boroughs. Of these, we have restricted the pool of buildings to contain only buildings managed by NYCHA. Further building inclusion/exclusion criteria are detailed below.

### Eligibility Criteria {10}

There are two sets of eligibility criteria: (1) building eligibility and (2) participant eligibility.

The first stage of enrollment occurs at the building level as the buildings are randomized to receive a designated intervention (A, B, A + B) or act as a control site. Buildings must (1) have more than 50 units and (2) not be undergoing major renovations. Buildings that belong to developments that are (1) not in Manhattan or the Bronx, (2), smaller than 50 units, (3) undergoing major renovations, (3) mixed finance, (4) exclusively for elderly, (5) privately managed, (6) or will be part of Rental Assistance Demonstration (RAD) or Permanent Affordability Commitment Together (PACT) are excluded. RAD and PACT programs are associated with increased funds towards repairs and investments in social programming that have the potential to influence the impact of the designed interventions (65, 66), and, thus, have been excluded (44).

Upon randomization, resident leaders will be informed of the study on a rolling basis. If a resident leader declines participation of their buildings and residents in the study, their buildings will be removed from the pool of eligible buildings. See Fig. 3 for the site selection process.

The second stage of enrollment is at the resident level. Participants must be (1) able and willing to provide verbal informed consent, (2) at least 18 years old, (3) able to communicate in English or Spanish, (4) living in the building at least 5 days/week and 9 months/year, and (5) not planning to move in the next 2 years. Participants who (1) have severe physical or mental medical conditions (e.g., cognitive disability) or other factors that could limit participation or ability to give informed consent in the study at baseline or during follow-up visits, (2) participate in focus groups conducted pre or concurrently as RCT that are geared towards understanding how to improve intervention arms for greater impact (buildings identified for focus groups are buildings that will not be assigned an intervention or have recruitment conducted for the main study), or (3) only smoke non-tobacco products (e.g., marijuana) are excluded from participating in the study due to the focus of the study on tobacco products. It should be noted that during the period of recruitment, the smoke-free policy in NYCHA was modified to also include marijuana use. In anticipation of this modification to the smoke-free policy, we are collecting preliminary information regarding marijuana use.

Recruitment of NYCHA residents will be conducted via door knocking and lobby intercepts until the targeted number per group is reached (4 smokers, 4 non-smokers in each building). Smoker status is defined as smoking a tobacco product including e-cigarettes at least 5x/month, and nonsmoker status is defined as never having smoked any product or quit smoking at least 12 months prior to recruitment.

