## Assignment of interventions: allocation

### Sequence Generation {16a}

A list of eligible buildings from each borough will be randomly ordered by computer-generated random numbers for each borough. Then, the first 24 buildings for each borough (n = 48, 24 per borough) will be randomly assigned to receive intervention A, B, or A + B.

Additionally, all buildings that are eligible for the study but have been identified by NYCHA as locations where they will conduct activities to promote the smoke-free policy will be randomly ordered by computer-generated numbers for each borough. Then, the first 8 buildings for each borough (n = 16, 8 per borough) will be assigned to serve as a control site.

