### Implementation {16c}

[name] oversaw the allocation sequence and intervention assignment prior to the start of recruitment. Trained field-based research support staff are recruiting and enrolling participants in buildings that are enrolled in the study.

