## Statistical methods

### Statistical Methods For Primary And Secondary Outcomes {20a}

We will conduct intent-to-treat (ITT) and contamination-adjusted intent-to-treat (CA-ITT) analyses to estimate the effects of the smoking relocation/cessation and resident endorsement interventions compared to the standard program implemented by NYCHA (no treatment). CA-ITT analyses will account for unanticipated contamination between trial arms and be completed via two-stage instrumental variables regressions using the original random allocation codes per assigned unit. Preliminary data analysis will include examination of distribution and summary statistics of all variables by intervention groups at each time point. The continuous variables with skewed distribution will be properly transformed, if necessary, to reduce impact of extreme values or improve model fitting. We will use box-plots to examine how distribution of a quantitative variable varies by categories of a categorical variable, and use scatter plots and Spearman correlation coefficient to examine bivariate associations between quantitative variables. Chi-square and Kruskal-Wallis tests will be used to detect group differences in categorical and quantitative baseline variables, respectively. For successful randomization, we expect no difference in the distribution of all baseline variables among the four arms. The baseline variables that differ by intervention groups and are related to outcomes of interest will be controlled in the aim specific models.

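### Resident leaders are asked after their building has been assigned to an arm, and a refusal removes it, so the buildings analysed are those that accepted, not those allocated

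*Protocol article*

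**What the plan says.** Five sections of the protocol article bear on the order of events.

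- **Eligibility Criteria {10}** describes the building stage: "The first stage of enrollment occurs at the building level as the buildings are randomized to receive a designated intervention (A, B, A + B"; acting as a control site is the remaining possibility. It continues: "Upon randomization, resident leaders will be informed of the study on a rolling basis". On refusal: "If a resident leader declines participation of their buildings and residents in the study, their buildings will be removed from the pool of eligible buildings".
- **Sequence Generation {16a}** starts from a borough list of buildings already called eligible: "the first 24 buildings for each borough (n = 48, 24 per borough) will be randomly assigned to receive intervention A, B, or A + B". For the standard arm, drawn from a separate list of sites where the housing authority plans its own activities, "the first 8 buildings for each borough (n = 16, 8 per borough) will be assigned to serve as a control site". Neither step mentions leader agreement.
- **Implementation {16c}** reports that the responsible person "oversaw the allocation sequence and intervention assignment prior to the start of recruitment".
- **Concealment Mechanism {16b}** restricts knowledge of the allocation to certain members of the research team and to the peer educators who deliver the programmes. Separately, it keeps data collectors uninformed.
- **Statistical Methods {20a}** promises an intention-to-treat analysis, and a contamination-adjusted one "using the original random allocation codes per assigned unit".

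The target is a "cluster RCT that targets 64 randomly selected buildings (16 buildings per arm) in separate NYCHA developments".

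**The concern.** A condition that a cluster must meet to be in the trial is tested after the cluster has its arm. A building removed at that point has an allocation code but no residents and no outcomes. An analysis by allocated arm therefore covers only the buildings whose leaders agreed.

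This matters most if the answer can depend on the arm, because the arms ask different things of a building. Endorsement (B, and A + B) brings building-wide sessions, pledges and door signage. Reduction/cessation (A) is work with individual enrolled smokers. The standard arm adds no programme. Leader receptivity could also be related to outcome, since the Background section links compliance to social ties and to relations with property management. If refusal depended on both the arm and such factors, even the comparisons among A, B and A + B would no longer compare like with like. A few selective refusals carry weight when an arm has 16 buildings.

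**Working it through.** **Count of allocated buildings.** From Sequence Generation, 2 × 24 + 2 × 8 = 48 + 16 = 64, and 48 / 3 = 16 per intervention arm. This matches Trial Design. The 64 are the allocated set. The article does not say how the number stays at 16 per arm once a leader declines.

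**Order of steps.** Eligibility Criteria uses randomisation to mean assignment to an arm and puts the leader contact after it. Implementation puts assignment before recruitment. Sequence Generation assigns from an eligible list with no agreement step, while Eligibility Criteria removes refusing buildings from eligibility afterwards. A building cannot both be eligible when assigned and have its eligibility settled by a later answer. Statistical Methods relies on the original allocation, which for a removed building has no data attached.

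**Possible shift if refusal depends on the arm.** The document gives no refusal rate, so these are assumptions:

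- a fraction q of buildings refuses in one arm and none in the comparator;
- refusing buildings lie at the low end of a normally distributed receptivity, whose correlation with the building component of outcome is r;
- the building component has standard deviation √ICC in units of the outcome SD, with ICC from the Sample Size section (0.1-0.2).

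Shift = r × √ICC × λ(q), where λ(q) = φ(z_q) / (1 − q). Replacement from the list leaves this unchanged if the replacements face the same filter.

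| q | λ(q) | ICC 0.1: r = 0.3 / 0.6 / 1 | ICC 0.2: r = 0.3 / 0.6 / 1 |
|---|---|---|---|
| 10% | 0.1755/0.9 = 0.195 | 0.018 / 0.037 / 0.062 | 0.026 / 0.052 / 0.087 |
| 20% | 0.2800/0.8 = 0.350 | 0.033 / 0.066 / 0.111 | 0.047 / 0.094 / 0.157 |
| 30% | 0.3477/0.7 = 0.497 | 0.047 / 0.094 / 0.157 | 0.067 / 0.133 / 0.222 |

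The range is about 0.02-0.13 SD for r = 0.3-0.6. It is 0.06-0.22 SD for r = 1, which is perfect sorting and an upper limit.

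**Benchmark.** The plan's smallest detectable effect is 0.283 SD, for the with/without-treatment contrast at ICC 0.1. The normal approximation (1.960 + 0.842) × √(2 × 1.3 / 256) = 0.282 reproduces it, but that needs 64 buildings of 4 per group. With the stated 16 buildings of 4 per arm, so 32 per group, it is 2.802 × √(2 × 1.3 / 128) = 0.399. A shift s in one arm moves the average of two pooled arms by s/2. It moves the pooled contrast by the full s only if both arms sharing a component are affected alike.

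**Cost if refusal does not depend on the arm and buildings are not replaced.** With 4 residents per building, ICC 0.1, α = 0.0167, 80% power and a t test on building degrees of freedom, the detectable difference between two arms is 0.685 SD at 16 buildings each. It becomes 0.738 SD at 14 and 0.806 SD at 12.

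**The case against.** **Leaders may be masked.** Concealment Mechanism restricts the allocation to a short list that does not include resident leaders, and Eligibility Criteria says that they hear of the study, not of the arm. If so, refusal need not differ by arm, and A, B and A + B stay randomised among consenting buildings. This stands as a limit: a reader might infer that bias is established, and the document does not support that. But no section states that leaders answer without knowing the arm.

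**Direction.** A reader might infer that hostile leaders would refuse the visible programme, leaving the endorsement arms with cooperative buildings. The document does not settle this. According to Intervention Description, tenant association members organised the pledge pilot and 85% of residents signed, so leaders may equally welcome endorsement.

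**Alternative reading.** Randomisation could mean only the random ordering of the list, with refusers struck out before assignment. The figures on site selection and enrolment, which might show this, are not available here. Against it, Eligibility Criteria itself ties the word to assignment, and Implementation places assignment before recruitment. Even on this reading the sections need reconciling.

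**Size and mitigation.** Every shift shown rests on assumed refusal in one arm only, and all lie below 0.283 SD. Adjustment for baseline variables that differ by arm could absorb part of a stable building difference. Both points stand, but adjustment cannot recover buildings with no data.

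**Timing.** Assignment is reported as done and recruitment as under way, so reordering the steps is not available for buildings already assigned. This stands and shapes the fix. An article may also leave a replacement rule or a contact script to the full protocol. The point therefore rests on the stated order of steps and not on those omissions.

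**Conclusion.** The concern holds as a statement about the set compared. Leader agreement operates as a post-randomisation eligibility criterion, the analysed buildings are those that accepted, and Eligibility Criteria, Sequence Generation and Statistical Methods do not fit together on this.

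Whether it biases anything depends on what leaders know when they answer. If they know the arm, refusal could differ by arm and distort the A, B and A + B comparisons, by about 0.02-0.13 SD under the moderate assumptions above and at most 0.06-0.22 SD under perfect sorting. Neither the refusal rate nor the direction can be taken from the document. If they do not know it, the consequences are fewer clusters and a narrower population of buildings.

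The point concerns the three randomised arms. Control buildings come from a different list, so contrasts with the standard arm are not randomised even with no refusals; that is a separate matter.

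**What to change.** 1. Wherever assignment can still follow it, obtain the leader's agreement first: work down the random order in each borough, record yes or no to taking part in any arm, and assign only buildings that agreed.
2. For buildings already assigned but not yet approached, record the leader's answer before the arm is disclosed, and say so in the protocol.
3. Replace a refusing building with the next on the same borough list, in the same arm slot. This protects the number of clusters. It does not protect against arm-dependent refusal, which is why step 2 is needed as well.
4. Report approaches and refusals by arm, including those that have already occurred, and state whether the leader knew the arm.
5. Define the intention-to-treat set of buildings, and keep in it any building that withdraws after its leader accepted.
6. Reconcile Eligibility Criteria with Sequence Generation, so that eligible has one meaning and one point in time.

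The cost is slightly more lead time and a script for the leader contact. Some leaders may decline an unspecified arm. Nothing here requires re-randomising buildings already in the trial.

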### Outcomes {12}

#### Primary Outcomes:

There are three primary outcomes being measured:

We will evaluate the change in number of cigarettes smoked per day using self-reported average number of cigarettes smoked per day among smokers measured at the time of baseline assessment, interim assessment (approximately 3 months post-intervention), and long-term assessment (approximately 12 months post intervention).We will evaluate change in salivary cotinine levels for 25% of the sample via passive drool collection among smokers and non-smokers collected at baseline assessment and the long-term assessment.We will evaluate change in secondhand smoke exposure via self-reported amount of exposure to secondhand smoke. This will be measured in all three assessments.

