#### Sample Size {14}

Power analysis was conducted using software PASS.15 for the primary outcome (change in salivary cotinine over a year) in Aims 1 and 2. Sampling 16 clusters (buildings) with 4 subjects per cluster (smokers for Aim 1, non-smokers for Aim 2) in each arm, we have 128 subjects per group or 256 in groups with or without a specific type of treatment (e.g. resident endorsement vs. no endorsement, cessation vs. no cessation). We calculated effect size as group mean difference in unit of standard deviation (SD) of the outcome, based on a two-sided test for mean difference between two groups in a cluster-randomized design with power of 80%. To compare groups with and without specific type of treatment, the group size of 256 may detect effect size of 0.283SD, 0.299SD, 0.312SD at significance level alpha = 0.05 for intra-cluster correlation coefficient r = 0.1, 0.15, 0.2, respectively. To compare intervention arms to the control arm, we have 3 comparisons and use conservative Bonferroni adjustment for multiple tests on significance level that alpha = 0.0167 (= 0.05/3). The sample size of 128 subject per arm may detect effect size of 0.472SD, 0.499SD and 0.524SD for r = 0.1, 0.15 and 0.2, respectively, at alpha = 0.0167. To put these numbers in perspective, using mean and SD estimated from a study of smokers in Maryland, an effect size of 0.283SD would correspond to a mean difference in salivary cotinine between the two intervention groups of 55.3 ng/mL with group SD = 195.4 ng/mL for smokers and of 0.19 ng/mL with group SD = 0.672 ng/mL for non-smokers.124 For instance a mean difference in 5 cigarettes smoked per day in the same study was 59.6 ng/mL for smokers.124 In England, following the smoke-free legislation salivary cotinine declined from mean level of 0.36 to 0.07 ng/mL (mean difference 0.29 ng/mL) among non-smokers.125 These findings support that we have sufficient power to estimate the impact of our interventions. The study is powered on an 80% retention rate, which we have achieved in other studies. Reasons for attrition will be tracked; those lost to follow up will be compared to the final sample.

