### Primary outcome

1)

Self-reported average number of cigarettes smoked per day and secondhand smoking exposure (hours of secondhand smoke exposure in the building in the past 7 days) will be measured at baseline (in person interview), 3 months (phone interview) and 12 months (in person interview). Salivary cotinine will be measured for 25% of the sample at baseline and at the 12-month follow-up for smokers to evaluate reliability of self-reported smoking behavior in Aim 1 and for non-smokers to evaluate self-reported secondhand smoke exposure in Aim 2.

To examine the intervention group differences in the change of self-reported smoking (Aim 1), we will use GLMRM with identity link, E(Yijkh) = ßh + ßkhtk + ßZij, where Yijkh is an outcome variable (transformed if necessary) for smoking exposure measured at time tk (t0 = 0 for baseline; t1 = 1 for 6 months, 0 else; and t2 = 1 for 1 year, 0 else) from the ith participant of the jth building in the hth arm/group (h = 1, 2, 3, 4). For the reference group of h = 4, ßk4 = 0 for k = 0, 1, 2; so that parameter ßkh (k = 1, 2; h = 1, 2, 3 for intervention arm) indicates the difference in outcome change since baseline between intervention group h and reference group, and ß is a vector of coefficients for the vector of control variables Zij (if any). To examine if effect of treatment A depends on treatment B or vice-versa, we will test null hypothesis ßk1 = ßk2 + ßk3 for all k, which suggests independent effects of treatment A and treatment B and simpler model that E(Yijk) = ß0 + ß1A + ß2B + ßk0tk + ßk1tk A + ßk2tk B + ßZij with dummy variables A and B indicating treatment type. To examine the intervention group differences in the change in hours of secondhand smoke exposure in the building in the past 7 days for non-smokers, we will use GLMRM with log link (Aim 2). Models will be run with and without control variables (if any).

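### The smoker stratum admits people who smoke no cigarettes, but the self-reported Aim 1 primary outcome is change in cigarettes per day among all smokers

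*Protocol article*

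**What the plan says.** Entry: Eligibility Criteria {10} states that "Smoker status is defined as smoking a tobacco product including e-cigarettes at least 5x/month". The only product-based exclusion is for people who "only smoke non-tobacco products (e.g., marijuana) are excluded from participating in the study". There is no minimum number of cigarettes and no requirement to smoke cigarettes at all.

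Outcome: the first primary outcome in Outcomes {12} is "change in number of cigarettes smoked per day using self-reported average number of cigarettes smoked per day among smokers", taken at baseline, about 3 months and about 12 months. The second is "change in salivary cotinine levels for 25% of the sample via passive drool collection among smokers and non-smokers", taken at baseline and the long-term assessment.

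Analysis: the statistical section headed Primary outcome says "To examine the intervention group differences in the change of self-reported smoking (Aim 1), we will use GLMRM with identity link". It names no restriction to cigarette smokers and no conversion for other products. The same section collects cotinine in 25% of the sample, "for smokers to evaluate reliability of self-reported smoking behavior in Aim 1". The sensitivity analyses then adjust the primary analyses for imperfect self-report by regression calibration. The secondary outcome of a successful quit does not say which product must be quit.

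**The concern.** Population and outcome are both fixed in the text, and they cover different products. Three things follow.

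- **Structural zeros.** An exclusive e-cigarette or cigar user starts at zero cigarettes per day and can only stay there or rise. Averaging over such people pulls every arm contrast toward zero. Very infrequent cigarette smokers can reduce, but only slightly, which is a floor effect.
- **Substitution scored as success.** A full move from cigarettes to e-cigarettes gives the largest possible fall in cigarettes per day, although the person would still be a smoker by the trial's own definition. Arms 1 and 3 encourage smokers to cut down, so switching could differ by arm. Part of an estimated effect could then be substitution.
- **Calibration.** The cotinine assay is described as measuring nicotine exposure. A participant who truthfully reports few or no cigarettes but takes in nicotine from another product looks like a misreporter when cigarettes per day is set against cotinine.

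Aim 1 asks about personal smoking behaviour. As written, the self-reported outcome measures that only for the cigarette part of it.

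**Working it through.** **The plan's own figures.** No figure is printed for the power of cigarettes per day. The Sample Size section powers the trial "for the primary outcome (change in salivary cotinine over a year) in Aims 1 and 2". Its 0.283 SD reproduces from 256 per group, 4 per building and an intra-cluster correlation of 0.1: (1.960 + 0.842) × √(2 × 1.3 / 256) = 0.282, or 0.283 with a t reference distribution. Then 0.283 × 195.4 = 55.3 ng/mL, as stated. These are cotinine figures, so nothing below corrects them.

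**Dilution of the mean difference.** Let p be the share of the smoker stratum at zero cigarettes per day at baseline. Assume p is equal across arms and that these participants stay at zero.

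Estimated difference = (1 − p) × D + p × 0 = (1 − p) × D, where D is the difference among cigarette smokers.

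Trial design gives 16 buildings per arm and 4 smokers per building, so 16 × 4 = 64 smokers per arm. The values of p are assumptions.

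| Assumed p | Zero-cigarette smokers per arm | Estimate as a share of D |
|---|---|---|
| 10% | 6.4 | 90% |
| 20% | 12.8 | 80% |
| 30% | 19.2 | 70% |

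**Floor effect.** The entry threshold counts occasions. At one cigarette per occasion (an assumption), 5 / 30 = 0.17 cigarettes per day, so such a person can fall by at most 0.17. This is the bottom of the eligible range, not a typical participant.

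**Switching.** A person who smokes c cigarettes per day and moves wholly to e-cigarettes has a change of 0 − c = −c, the same score as someone who stops all products. The entry definition still calls the first person a smoker.

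**What cotinine can show.** The subsample is 25% of 512 = 128 people, or 32 per arm. If split evenly by smoking status (an assumption), that is 16 smokers per arm. Three quarters of the sample has no biomarker against which to see a switch.

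**Is power the main loss?** Take a reference contrast with 80% power at alpha 0.05, and let the zero-cigarette participants contribute no change. The SD of change then shrinks by about √(1 − p), so the standardised effect is multiplied by (1 − p) / √(1 − p) = √(1 − p).

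- Diluted analysis: power = Φ(2.802 × √(1 − p) − 1.960) = 76%, 71%, 65% for p = 10%, 20%, 30%.
- Restricted analysis: n(1 − p) participants, 4(1 − p) per building, intra-cluster correlation 0.1, so power = Φ(2.802 × √[(1 − p) × 1.3 / (1 + (4(1 − p) − 1) × 0.1)] − 1.960) = 77%, 73%, 69%.

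Restriction regains about 1 to 4 points. What it mainly changes is the estimate, from (1 − p)D back to D.

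**The case against.** **Cotinine is also primary.** It is listed among the three primary outcomes and measures nicotine exposure, so the trial as a whole does not score a switch to vaping as success. That stands as a limit on the point. It does not remove it: cotinine covers a quarter of the sample, and the analysis section uses it to check self-report.

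**The questionnaire and a separate analysis plan are not shown.** Either might count e-cigarettes or set product rules. But the outcome is worded as cigarettes among smokers, and the smoker definition is explicit. A later document that bridged them would be changing what is written here.

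**Broad entry suits a policy trial.** It does, and eligibility need not change.

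A reader might go further in four ways that the protocol does not support.

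- *That people using tobacco 5 times a month cannot reduce.* This holds only for those who smoke no cigarettes.
- *That the sample size describes a different population.* Setting 55.3 ng/mL against the statement "For instance a mean difference in 5 cigarettes smoked per day in the same study was 59.6 ng/mL for smokers" gives 55.3 / 59.6 × 5 = 4.6 cigarettes per day. But power is computed on cotinine, the cigarette figure is offered only as an illustration, and no distribution of cigarette counts among eligible residents is given.
- *That power falls from 80% to 71%, 61% or 50%.* Those values come from Φ(2.802 × (1 − p) − 1.960), which keeps the SD unchanged. People fixed at zero add almost no variance to change, and p is unknown.
- *That nicotine patches invalidate the cotinine check.* The supply lasts one month, and follow-up cotinine is taken about 12 months after the intervention. Continuing use of other nicotine products is the more relevant source of error, and its frequency is unknown.

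**Conclusion.** The point holds. The smoker stratum and the self-reported Aim 1 primary outcome cover different products, and nothing in the protocol connects them. The estimated difference in cigarettes per day shrinks in proportion to the share of participants who smoke no cigarettes at baseline. That share is not documented, so 10% to 30% is illustration only. The proportional result assumes the share is equal across arms and that these participants do not take up cigarettes.

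A full switch to e-cigarettes counts as the maximum reduction on this outcome. For the quit outcome the treatment of switching is open, because no product is named; false success there is not shown. Non-cigarette nicotine adds error to the cotinine calibration, by an amount that cannot be stated. The protocol does not support a definite power loss, or a claim that the trial was planned for other people.

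**What to change.** Leave eligibility unchanged and make four changes.

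1. Define the cigarettes-per-day analysis set as smokers who report any cigarette smoking at baseline. The baseline interview follows building allocation but precedes intervention delivery by about a month, so the intervention cannot influence who is in the set.
2. Keep the other smokers for the secondhand-smoke outcomes, and for a supportive Aim 1 outcome that covers all tobacco products and e-cigarettes.
3. State that a switch to e-cigarettes is continued use, both in that supportive outcome and in the quit outcome.
4. Record non-cigarette nicotine use at each cotinine collection and account for it in the regression calibration.

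Cost: somewhat fewer participants in the cigarettes-per-day analysis, and a few product-use items in the questionnaire if it lacks them. In buildings already enrolled, the baseline product items need to be available for the set to be defined. Raising the entry threshold during recruitment is not needed, and would give early and late buildings different smoker populations.
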